## Abstract

**Introduction:**

Hepatocellular carcinoma (HCC) is expected to become the third most common cause of cancer death worldwide by 2030. The increase in HCC is in large part due to the rising prevalence of risk factors such as type 2 diabetes mellitus (T2DM). Up to 1 in 20 people living with T2DM have liver cirrhosis, and they have a 1% to 2% incidence of HCC per year. Patients with cirrhosis enter surveillance for HCC to identify early-stage, curable tumours. A diagnosis of T2DM does not mandate testing to identify patients with cirrhosis, with testing restricted to those with additional risks. There has never been a trial and nested cost-effectiveness evaluation comparing screening all patients with T2DM for cirrhosis against usual care.

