However, there are challenges with extrapolating prior models to a real-world intervention such as the NHSE pilot that aims to test a broader range of adults with T2DM for liver disease as part of routine care. First, we do not know the characteristics of patients who will respond to an invitation from primary care for liver assessment. These characteristics are important—it is likely that patient age and comorbidities will influence their probability of having liver disease and their personal gain from an early diagnosis. Second, we do not know what proportion of this cohort meets clinical criteria for interventions that convey the advantage of early diagnosis, for example, what proportion enter an HCC surveillance pathway and what proportion have clinically significant portal hypertension and are started on beta blockers. Third, we do not know the real-world performance of standard care in the UK. Most patients with T2DM do not get tested for liver disease, despite their heightened risk because they are not assessed for the additional risk factors that are needed to qualify for testing. For example, LFTs are not part of an annual diabetes check-up in the UK and may or may not be measured when patients are considered for statin treatment; liver ultrasound is not a routine test, and alcohol consumption is not accurately or consistently assessed in primary care. Finally, previous economic evaluations are outdated as they use primary-care-based assessments (eg history and examination) that do not incorporate tests for fibrosis (eg Fib-4 and VCTE). Since the NICE NAFLD Guideline in 2016, tests for liver fibrosis have widely integrated into community diagnostic pathways for liver disease and therefore in future studies, models of ‘usual care’ need to reflect this.

This study protocol describes a randomised controlled trial with a nested cost-effectiveness evaluation. The study aims to compare the number of participants referred for HCC surveillance between an intervention where patients with T2DM are universally offered screening for liver disease against usual care.

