## Method and analysis

The trial is described in accordance with the SPIRIT checklist.^37^ The design will be an unblinded randomised controlled trial with a nested cost-effectiveness evaluation comparing the offer of screening to *all* patients with T2DM for liver disease against standard care. We will proceed straight to an effectiveness evaluation rather than conducting a formal feasibility/pilot study. We justify this approach because the components of the intervention (used in testing for liver disease in patients with standard risk factors (eg abnormal blood results or harmful alcohol consumption)) are widely implemented. Additionally, data such as the attrition rate from the conventional diagnostic pathway is already known (see sample size section).^38^ Undertaking a randomised controlled trial in this setting is very important as this provides a contemporaneous standard care arm as a counterfactual.

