#### Cost-effectiveness analysis

For the cost-effectiveness evaluation, data from the study will be incorporated into a decision analytical model (developed in Microsoft Excel). These data include: the micro-costs of testing and follow-up, drop-out rates from the diagnostic pathways (usual care and screening), the relative proportions of different stages of liver disease and the demographic characteristics of the cohorts.

The model will consist of a decision tree for the diagnostic process and a Markov state transition model for the long-term disease process (figure 2). It will estimate the quality-adjusted life years (QALYs) and costs associated with liver disease. The model structure will be similar to previous models for HCC surveillance (eg,^34 36^) and calculate the difference in costs and QALYs between different testing approaches and no testing. Patients with characteristics based on our study population and study outcomes will enter the model. The model will have 1 year cycles and a lifetime horizon (ie until the cohort age is 100 years). Costs will be calculated using an NHS and Personal Social Services perspective. Costs and utilities for the model health states will be taken from a targeted review of the medical literature.

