**Figure 2 F2:**
[figure not shown]
Markov model structure is used to calculate the incremental cost-effectiveness of different testing strategies. The findings from the trial will parameterise this model. Numbers 1–4 correspond to the benefits of early detection that will be incorporated into the modelling. HCC, hepatocellular carcinoma.

Our base-case analysis will closely match real-world practice. In both cohorts, patients identified with liver cirrhosis and referred for HCC surveillance will enter a separate health state—named F4_SURV. Based on recently published data, participants in this health state who develop HCC will have a higher chance of cure (ie return to their original F4 SURV health state) and a lower chance of progression to death or transplantation.^16^ Similarly, a proportion of those in F4_SURV will have a lower risk of progressing to a decompensated state that reflects the real-world number of participants who commence B blockers by recent guidelines.^45 46^ Participants identified with F2 or F3 disease will enter monitoring states (F2_Mon and F3_Mon) and undergo biannual assessment for progression to F4 disease. Monitoring will stop when participants in the model reach 80 years of age.

As part of our base case analysis, we will calculate the cost-effectiveness (cost per QALY) of four testing strategies that are broadly reflective of current testing strategies in the study region and the NHSE pilot (described in the background). These will be compared against ‘no testing’ and presented as ICERs that can then be compared between strategies.

Usual care.Reflex testing with VCTE only (ie everyone offered VCTE).FIB-4 then VCTE for patients with FIB-4>3.25.ELF then VCTE for patients with an ELF >9.5.

We will conduct probabilistic sensitivity analyses where model parameters are probabilistically varied across pre-specified distributions and ranges. The results of the probabilistic sensitivity analyses will be presented as a scatter plot and a cost-effectiveness acceptability curve.

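### The base case sets four mutually exclusive strategies, usual care among them, against 'no testing' and then compares the ICERs; these ratios cannot identify the cost-effective strategy, and usual care is not named as comparator

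*Protocol article*

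**What the plan says.** Under Cost-effectiveness analysis, the protocol article says that the model will "calculate the difference in costs and QALYs between different testing approaches and no testing". In the text after Figure 2 it adds that, in the base case, "we will calculate the cost-effectiveness (cost per QALY) of four testing strategies". The four are usual care, VCTE offered to everyone, FIB-4 followed by VCTE above a cut-off, and ELF followed by VCTE above a cut-off. The comparator and the use of the results come next: all four are set against 'no testing', and the results are "presented as ICERs that can then be compared between strategies".

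Other sections give the evaluation a different reference point. The Abstract describes the missing evidence as a trial and "nested cost-effectiveness evaluation comparing screening all patients with T2DM for cirrhosis against usual care". The Introduction closes by setting "an intervention where patients with T2DM are universally offered screening for liver disease against usual care". Method and analysis justifies randomising because "this provides a contemporaneous standard care arm as a counterfactual". The secondary outcomes list an ICER of screening without naming its comparator.

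**The concern.** The four strategies are alternatives: adopting one for a population means not adopting the others. The relevant quantity is therefore the extra cost per extra QALY of each strategy over the best alternative that it would displace. A ratio against 'no testing' spreads a strategy's whole cost over its whole gain, including the part that a cheaper strategy would already deliver. Two errors can follow. Picking the lowest ratio can favour a small, cheap strategy when a better one is worth its extra cost. Checking each ratio separately against a threshold can pass a strategy whose last increment is far too expensive.

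'No testing' is also not a trial arm. The arm randomised as counterfactual, usual care, becomes one more option measured against a hypothetical baseline.

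The results go directly to National Health Service England, and the Discussion says that they could justify or prevent wide rollout. The strengths list also promises the relative cost-effectiveness of the different non-invasive tests, which is a comparison between strategies.

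**Working it through.** **Inputs.** The article gives no cost, QALY or ICER for this trial and refers to thresholds without a figure, so there is nothing to reproduce. All numbers below are assumptions that show how the method behaves. C and Q are cost and QALY gain per person relative to 'no testing'.

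**Formulas.** Ratio against 'no testing': C/Q. Sequential ratio against the next cheaper strategy on the frontier: (C_j − C_i)/(Q_j − Q_i). Net benefit at threshold λ: λQ − C.

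**Illustration 1.**

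| Strategy | C (£) | Q | Against 'no testing' | Against next cheaper |
|---|---|---|---|---|
| Usual care | 20 | 0.004 | 5,000 | 5,000 |
| FIB-4 then VCTE | 60 | 0.010 | 6,000 | 40/0.006 = 6,667 |
| ELF then VCTE | 150 | 0.020 | 7,500 | 90/0.010 = 9,000 |
| VCTE for all | 500 | 0.028 | 17,857 | 350/0.008 = 43,750 |

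At an assumed £20,000 all four pass against 'no testing', but VCTE for all fails against ELF then VCTE. The same disagreement holds for any threshold between £17,857 and £43,750. VCTE for all against usual care is (500 − 20)/(0.028 − 0.004) = £20,000.

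The reversal depends on the assumed £500. With the other inputs fixed and a £20,000 threshold, VCTE for all passes the sequential test if its cost is below 150 + 20,000 × 0.008 = £310; at £300 it is 150/0.008 = £18,750. It passes against 'no testing' up to 20,000 × 0.028 = £560. The two methods therefore disagree between £310 and £560 and agree outside that range.

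**Illustration 2** (three strategies, other assumed inputs): usual care (20; 0.010), FIB-4 then VCTE (60; 0.014), VCTE for all (200; 0.018).

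- Against 'no testing': 2,000, 4,286 and 11,111.
- Sequential: 2,000; 40/0.004 = 10,000; 140/0.004 = 35,000.
- VCTE for all against usual care: 180/0.008 = 22,500.
- Net benefit at λ = 20,000: 180, 220 and 160. FIB-4 then VCTE is best here and at 15,000, 25,000 and 30,000; VCTE for all is best at 40,000.

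The lowest ratio would select usual care, although FIB-4 then VCTE adds QALYs at 10,000 each. A separate check of each ratio at 20,000 would pass VCTE for all, although it costs 22,500 per QALY over usual care.

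**Can screening versus usual care be recovered from the ratios?** Let R_S and R_U be the ratios of screening and usual care against 'no testing', and q = Q_U/Q_S. Since C_S = R_S·Q_S and C_U = R_U·q·Q_S, the ICER of screening against usual care is (R_S − q·R_U)/(1 − q). It depends on q, which the two ratios do not contain.

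| q | R_S = 12,000, R_U = 6,000 | R_S = 12,000, R_U = 2,000 |
|---|---|---|
| 0.02 | 12,122 | 12,204 |
| 0.10 | 12,667 | 13,111 |
| 0.25 | 14,000 | 15,333 |
| 0.50 | 18,000 | 22,000 |
| 0.80 | 36,000 | 52,000 |

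With the model's cost and QALY totals, q is known and the contrast follows by subtraction. When q is small, the choice of baseline hardly matters for this contrast.

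**The case against.** A reader might infer that the trial will never report screening against usual care. The documents do not support that. Usual care is one of the modelled strategies, and the common baseline cancels when two strategies' totals are subtracted. The Abstract and Methods commit to the contrast, and the secondary outcomes list an ICER of screening. What stands is narrower: the base-case text does not name usual care as comparator, and the ratios it does specify are not enough to obtain the contrast.

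It can also be said that the sentence sets no decision rule, that it describes only part of the base case, that Figure 3 is not visible, and that dominance, net benefit and the construction of the acceptability curve usually sit in a fuller economic plan. The absence of those details is indeed no fault in an article. But the comparator, and the use of the ratios for comparison between strategies, are stated rather than omitted, and a fuller plan that followed this text would carry the problem forward. Neither the Figure 2 caption's mention of incremental cost-effectiveness nor an acceptability curve of unstated construction changes the stated comparator.

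The objection on size is sound. Every input is assumed, and the reversal in Illustration 1 disappears at a lower cost for VCTE for all. On those inputs the trial's own contrast moves only from £17,857 to £20,000, a 12% shift. The Introduction says that most people with T2DM are not tested for liver disease, so usual care may be close to 'no testing'. That limits the error for screening versus usual care. It does not protect the comparison among the three screening strategies.

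**Conclusion.** The concern holds as a fault in the stated method. ICERs computed against a shared 'no testing' baseline do not identify the cost-effective option among mutually exclusive strategies and do not give the cost per extra QALY between them. The base case also leaves out usual care as named comparator, at odds with the purpose stated elsewhere in the article.

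The size is unknown. The illustrations show that a strategy can be under a threshold against 'no testing' and over it against the next-best strategy; they do not show that this will happen here. For screening versus usual care the shift may be negligible (about 1% to 2% at q = 0.02 in the examples) or large (a tripling or more at q = 0.80), depending on how many QALYs usual care yields. The point concerns a secondary, modelled outcome. It does not touch randomisation, data collection, sample size or the primary analysis, and it can be corrected at any time before the economic results are reported.

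**What to change.** Replace the sentence on comparison with 'no testing' by a fully incremental analysis:

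- Order all strategies by cost, remove dominated and extendedly dominated ones, and report each ICER against the next-best remaining strategy. Net benefit across all strategies is an equivalent way to identify the preferred option.
- Name screening versus usual care as the headline ICER, and add usual care as comparator to the ICER in the secondary outcomes list.
- Keep 'no testing' only as a reference strategy.
- Build the acceptability curve on net benefit over all strategies jointly.

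The sentence on cost and QALY differences earlier in the same section should be aligned with this. The cost is a few lines of wording and a different calculation on the same model outputs, with no new data or model runs. The downside is that some strategies may look less favourable than they would against 'no testing'.

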### Primary outcome

The number of participants referred to secondary care with the suspected liver disease within 12 months of randomisation who are subsequently referred for HCC surveillance.

As an unblinded trial, it is important our primary outcome is as objective as possible and independent of the research team. In both study arms, patients with high liver stiffness measurements will be referred to nearby hepatology services (with thresholds defined by local practice). Via usual care, an independent local clinician will then assess the severity of liver disease. In real-world practice, this may include history, examination, no further tests or repeat VCTE, additional tests for fibrosis and in some cases liver biopsy. Regardless of the clinical approach taken, the primary outcome will be whether the clinician felt the disease was severe enough to warrant referral for HCC surveillance. Since the trial sites cover a variety of different regions across the south of England, this pragmatic approach is likely to closely reflect current UK practice.

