### Secondary outcomes

The test or combination of tests for liver cirrhosis with the lowest cost per case diagnosed.*The sub-group with the lowest cost per case diagnosed.*The ICER of screening for liver cirrhosis in people with T2DM.The number of cancer deaths avoided by screening (as per Markov modelling).The number of patients diagnosed on VCTE with ≥F2 disease (defined as a liver stiffness of ≥8.2 kPa).^21^

*See (i) for the definition of a ‘case’.

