### Arm 1—screening

Participants in this arm will be referred by the research team directly for liver fibrosis assessment at a community hub. This assessment will include VCTE and venepuncture for an ELF test and a FIB-4 index. The result of the VCTE and any abnormalities identified in the blood tests will be managed by the local liver disease care pathway (as per the usual care arm described below). VCTE will be performed by an experienced single operator after a minimum of a 3-hour fast and previously published criteria for a valid reading will be applied to each participant.^40^

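### The screening ICERs are set against no testing rather than usual care, and no modelled strategy is the Arm 1 package as delivered

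*Protocol article*

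**What the plan says.** Under Secondary outcomes, the protocol article lists "The ICER of screening for liver cirrhosis in people with T2DM" without naming a comparator. The Abstract and the opening of the methods section do name one: both describe an evaluation of screening all people with T2DM against usual (standard) care.

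The Cost-effectiveness analysis section states: "As part of our base case analysis, we will calculate the cost-effectiveness (cost per QALY) of four testing strategies". The four are usual care; "Reflex testing with VCTE only (ie everyone offered VCTE"; FIB-4 followed by VCTE above a cut-off; and "ELF then VCTE for patients with an ELF >9.5". On the comparator it says: "These will be compared against ‘no testing’ and presented as ICERs that can then be compared between strategies". The general description of the model earlier in that section likewise sets the testing approaches against no testing.

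On what Arm 1 receives, the Arm 1 section says: "This assessment will include VCTE and venepuncture for an ELF test and a FIB-4 index". It adds that, besides the VCTE result, "any abnormalities identified in the blood tests will be managed by the local liver disease care pathway". The Primary outcome section describes the referral trigger in terms of stiffness: "In both study arms, patients with high liver stiffness measurements will be referred to nearby hepatology services".

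**The concern.** There are two separate problems.

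**Comparator.** No testing is not a trial arm. The trial randomises screening against usual care, and the methods section stresses the value of a contemporaneous standard care arm as the counterfactual. If every strategy is turned into a ratio against no testing and the ratios are then set side by side, the cost per additional QALY of replacing usual care with screening is not among the reported quantities. That is the figure a commissioner needs, and the results are to go directly to NHS England.

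**Intervention.** Arm 1 gives all three tests to everyone. None of the four strategies does so. The article does not say which strategy stands for Arm 1, or how outcomes observed after three tests are carried into a strategy that uses one test or two in sequence.

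**Working it through.** The documents give no cost, QALY or ICER, so there is no figure of the plan's own to reproduce. The check is a comparison of the text plus arithmetic on assumed values.

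**1. Does comparing ratios against no testing give the ratio of screening against usual care?**

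Let Cu and Qu be the extra cost and QALYs of usual care over no testing, and Cs and Qs those of screening over no testing.

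- Ratios as planned: Ru = Cu/Qu and Rs = Cs/Qs.
- Ratio for the trial's question: (Cs − Cu)/(Qs − Qu).
- Since Cs = Rs × Qs and Cu = Ru × Qu, the second equals Rs + (Rs − Ru) × Qu/(Qs − Qu).

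With Qs greater than Qu, the two coincide only if Rs = Ru or Qu = 0. If Rs exceeds Ru, the planned figure for screening is lower than the true incremental ratio; if Rs is below Ru, it is higher.

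Illustration (all values assumed, per person, against no testing): usual care +£20 and +0.004 QALY; VCTE for all +£150 and +0.015 QALY.

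- Usual care against no testing: 20/0.004 = £5,000.
- VCTE for all against no testing: 150/0.015 = £10,000.
- VCTE for all against usual care: (150 − 20)/(0.015 − 0.004) = 130/0.011 = £11,818.

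The two planned ratios do not fix the third. Keep usual care as above and let VCTE for all be +£200 and +0.020 QALY. The planned ratios are again £5,000 and £10,000 (200/0.020), but the ratio against usual care is 180/0.016 = £11,250.

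**2. What might the cost of the other two tests do?**

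Add an assumed £20 to £80 per person for ELF and FIB-4 to the first example, with no change in QALYs:

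- (170 − 20)/0.011 = £13,636.
- (230 − 20)/0.011 = £19,091.

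Over the assumed range (VCTE for all £100 to £200, gain 0.015 to 0.020 QALY, added test cost £0 to £80), the ratio against usual care runs from (100 − 20)/0.016 = £5,000 to (280 − 20)/0.011 = £23,636. This shows that the choice of branch and comparator can matter. It does not estimate this trial's result.

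**3. Arm 1 beside the strategy list**

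| | VCTE | ELF | FIB-4 |
|---|---|---|---|
| Arm 1 as delivered | all | all | all |
| Usual care | if risk factors present | varies | varies |
| VCTE-only | all | none | none |
| FIB-4 then VCTE | if FIB-4 above cut-off | none | all |
| ELF then VCTE | if ELF above cut-off | all | none |

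No strategy row matches the first. VCTE-only is nearest, because everyone is offered VCTE and referral is described as following high stiffness. Two routes remain by which blood results could affect Arm 1 outcomes. Abnormal results are passed to the local pathway. And the primary outcome rests on a clinician's later judgement about surveillance, which the Primary outcome section says may draw on additional fibrosis tests; ELF and FIB-4 results would by then exist.

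**The case against.** The strongest reply has four parts.

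- **The ratio can be derived.** Usual care and VCTE for all are both modelled for cost and QALYs, so their incremental ratio follows by subtraction. The list is introduced as part of the base case, and the ICER of screening remains a secondary outcome. This stands against the inference, which a reader might draw, that the ICER of screening over usual care will never be calculated. It does not rescue the stated method, which compares ratios against no testing.
- **VCTE-only is a fair counterpart of Arm 1.** Referral follows high stiffness, and the Arm 2 section says usual pathways in all areas involve VCTE. An abnormal blood result may therefore simply lead to a test that Arm 1 has already had. No text describes referral on blood results alone. This largely stands, although the Arm 1 wording does not rule out a contribution from the blood tests.
- **Three tests serve a research purpose.** Giving all three to the same people lets the tests be compared, which is a stated aim. Costing VCTE-only without ELF or FIB-4 is then correct, provided its cases are also those that VCTE alone would find. This stands, and it is the basis of part of the fix.
- **The link may be shown elsewhere.** Figure 3 is said to show how the arms and the economic evaluation connect, and it is not available here. Some mapping detail also belongs in a health-economics plan. This limits what can be said about the mapping. It does not affect the comparator, which the text states outright.

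**Conclusion.** The point holds in two parts.

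The comparator is fixed badly. Following the stated rule exactly yields ratios against no testing, and these are not the incremental ratio of screening over usual care that the article describes as its question. This follows from algebra and needs no assumed figure. The size of the gap depends on costs and QALYs that the documents do not give; £10,000 against £11,818 is an illustration only.

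The Arm 1 package is absent from the strategy list, and the text does not say which strategy represents it. This is the lesser part, because VCTE-only is a close counterpart.

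A reader might go further and conclude that the VCTE-only ICER will be flattered by setting a three-test effect against a one-test cost. The documents do not support that. Nothing says that undifferentiated Arm 1 outcomes feed that strategy, and there is no source for how many referrals, if any, would rest on blood results alone. Neither the size nor the direction of any bias in that ICER can be determined.

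**What to change.** - Define the secondary-outcome ICER as the difference in cost over the difference in QALYs between screening and usual care as observed in Arm 2.
- Report all strategies in a full incremental analysis: order them by cost, remove those that are dominated, and compare each with the next. Keep no testing as an additional reference only.
- Add a branch for Arm 1 as delivered, using the ELF, FIB-4, venepuncture and VCTE costs already listed under Cost data collection.
- Build VCTE-only, FIB-4-then-VCTE and ELF-then-VCTE from individual Arm 1 results, counting a case under a strategy only if that strategy's own rule would have found it. Record at extraction which result prompted each referral.

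The cost is one extra branch and a recalculation in the same Excel model, plus one extraction field. No further patients or tests are needed, and clinical management does not change.
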